## Study methods and analysis

### Overview of the study design and timeline

To evaluate the RISE intervention, we are conducting a cluster RCT involving 12 informal settlements in Suva, Fiji, and 12 in Makassar, Indonesia, with clustering at the settlement level. In each country, half of the sites have been randomised as intervention communities and will receive an early upgrade. The remaining communities will serve as controls and will receive only standard, basic hygiene and sanitation messages. Monitoring and assessment will be conducted in all settlements over an approximate 5-year timeline, which will include baseline data collection, the design and build implementation phase of the project, and 2 years of post-build monitoring (figure 2). After completion of the study, the intervention will be implemented in the 12 control settlements.

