### Sample size

The choice of 12 settlements per city, each of ~55 dwellings with five to six people per dwelling, has been made to balance the need for statistical power with the constraints of construction logistics and cost. Statistical power was calculated using formulae for cluster RCTs with repeated assessments of a cohort^95^ (and confirmed by numerical simulation using generalised linear mixed models) for the three primary health outcomes assessed in children aged under 5 years: (1) prevalence of gastrointestinal pathogens and diversity (number of bacterial, viral and parasitic gastrointestinal pathogens per sample); (2) diversity and abundance of AMR markers and (3) concentration of intestinal inflammation markers. For measures of diversity and abundance of markers of drug resistance in environmental samples, the power calculations assumed the same intracluster correlations as for the health outcomes (see below).

For the health outcomes involving subsampling of an average 30 children under 5 years of age per settlement, there is 80% power to detect, from 6-month postconstruction and beyond, a 40% relative reduction in the prevalence of gastrointestinal pathogens (assuming a baseline prevalence of 25%) and a 31% relative reduction in the average count of enteric pathogens per child (assuming a baseline average count of 1.0 and overdispersion factor of 2; with a baseline of 2.0 the relative reduction is 23%), and at 12 months an absolute difference of 0.30 SDs (and 0.34 SDs for environmental assessments) in the average concentration of intestinal inflammation markers and average number and abundance of AMR markers. These calculations assume intracluster (ie, within-settlement) correlations between: two children within the same time period 0.10^7^; two children in different time periods 0.067; and repeated measurements of the same child 0.10. The relative reduction of 30% has been informed by the findings reported in systematic reviews, which have found reductions of 30%–50% due to water quality interventions.^96 97^

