### Statistical analyses

Analyses will be by intention to treat. Descriptive statistics will report characteristics of settlements and of individuals by randomised arm. Estimation of the effects of the intervention for each outcome will use generalised estimating equations with an exchangeable correlation structure and robust standard errors clustered at settlement level, scaled with a small-sample degrees-of-freedom adjustment.^98^ Data from 6-month, 12-month, 18-month and 24-month follow-up visits will be included in the analysis and the intervention effect estimated for the 6-month follow-up timepoint for prevalence and mean number of gastrointestinal pathogens, and at 12-month follow-up for diversity and abundance of AMR markers and for intestinal inflammation markers. For binary and count outcomes, we will use a logarithmic link to estimate ratios of prevalence and mean counts, respectively; for continuous outcomes, the identity link will be used to estimate differences in means. All models will adjust for the baseline covariates, number of children under 5 years, flood risk category (see Randomisation section) and asset score. To enable temporal adjustment, indicator variables for seasonal patterns (eg, rainy vs dry), local rainfall data for each site and an indicator term for any major flood event at a particular settlement in a particular quarter will be included in the models. For households that drop out of the study, we will employ multiple imputation using imputation models that preserve the hierarchical data structure. Additional sensitivity analyses will exclude households who moved into the settlement postconstruction. There will be no adjustment to the p values for the assessment of multiple primary health outcomes; however, all findings will be fully reported and interpreted based on incremental evidence.

We will explore relationships between environmental changes and health outcomes by modelling health outcomes at 12-month, 18-month and 24-month postconstruction, using changes in environmental measures at 6-month, 12-month or 18-month postconstruction, respectively, as principal covariates. We will estimate these effects using generalised estimating equations with preconstruction health and environmental parameters as baseline covariates aggregated at settlement-level and will include interactions of environmental changes with the intervention for effect-modification assessment, together with adjustment for potential confounders.

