### Limitations, justifications and additional analyses

Water and sanitation trials aiming for community-level intervention coverage pose great challenges for trial designers.^99^ The relative lack of RCTs of such interventions reflects multiple inherent difficulties, including randomly allocating networked infrastructure, the long follow-up and large sample sizes required to study health outcomes and the need for a complex engineering and construction phase.^13^ The RISE study will deliver site-specific and bespoke interventions to each settlement, and while this is deliberate and a strength of our approach as it will address site-specific needs, it also results in a lack of intervention uniformity across communities. The purposive selection of settlements included and the relatively small size of each community compared with many informal settlement settings, while necessary from a logistics perspective, also limits broad external validity. Furthermore, while we intend to monitor the sustainability of the intervention, the RCT is funded to perform formal monitoring for an initial 2 years postintervention delivery.

Complete settlement revitalisation should ideally encompass a broad suite of measures incorporating comprehensive upgrading of solid waste management; improvements in housing conditions, roads, street lighting and other amenities in communal areas; and delivering a range of other services. However, to test our specific hypothesis (and given logistic and financial constraints), our planned site-specific intervention is restricted in scope to addressing many of these issues predominantly as they relate to our primary focus of delivering improved water and sanitation infrastructure and reduced flooding impacts, in order to minimise human exposure to environmental faecal contamination. For example, attention to solid waste management is important to ensure that the wetlands, which treat the wastewater on-site, will function as expected and not become blocked with solid waste, as this would reduce the ability of wetland plants to remove contaminants from the wastewater and potentially become a breeding site for vectors (ie, mosquitoes).

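### The pathogen effect is targeted at the 6-month visit, but the stated 80% power fits an effect averaged over 6 to 24 months, and the model does not say which is meant

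*Protocol article*

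**What the plan says.** The protocol article, Statistical analyses, first lists the data for the model: "Data from 6-month, 12-month, 18-month and 24-month follow-up visits will be included in the analysis". It then names one target visit per primary outcome. For pathogens this is "the intervention effect estimated for the 6-month follow-up timepoint for prevalence and mean number of gastrointestinal pathogens". For antimicrobial resistance (AMR) and inflammation the effect is estimated "at 12-month follow-up for diversity and abundance of AMR markers and for intestinal inflammation markers". Neither a constant arm effect nor arm-by-visit terms are mentioned.

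The Sample size section describes the pathogen effect differently: "there is 80% power to detect, from 6-month postconstruction and beyond, a 40% relative reduction in the prevalence of gastrointestinal pathogens". The starting value for that calculation is given in the same sentence ("assuming a baseline prevalence of 25"%).

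The design includes "2 years of post-build monitoring" (Overview of the study design and timeline). The one health analysis the article names at the later visits is the exploratory work "modelling health outcomes at 12-month, 18-month and 24-month postconstruction" on earlier environmental changes. Its principal covariate arises after randomisation and it adjusts for confounders, so it is not a randomised comparison of the arms.

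**The concern.** A repeated-measures model can yield two different quantities from these data. With a single arm coefficient, the estimate is a weighted average over 6 to 24 months, and calling it the 6-month effect is wrong unless the effect does not change. With arm-by-visit terms, the 6-month effect rests on the 6-month round (plus baseline adjustment), and the later rounds add almost nothing to its precision. The two have different meanings and very different power.

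At stake is how the main result is read. As an assumed illustration, suppose the prevalence ratio drifts evenly from 0.60 at 6 months to 0.80 at 24 months. The constant-effect model would report about 0.70 as the 6-month result; the visit-specific model would report about 0.60, with much less power than stated. Two analysts following the same text could give different primary answers.

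**Working it through.** **Inputs from Sample size and Randomisation.** 30 children per settlement on average; 12 settlements per arm; prevalence 25% with a 40% relative reduction, hence 15%; correlation 0.10 for two children in the same period, 0.067 for two children in different periods, 0.10 for the same child over time.

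**Assumed, because not stated.** Two-sided 5%, equal settlement sizes, no dropout, and the number of baseline stool rounds (varied from 0 to 2).

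**Step 1: clustering.** Design effect = 1 + 29 × 0.10 = 3.9. Correlation between settlement means at two visits: r = (0.10 + 29 × 0.067)/3.9 = 0.524.

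**Step 2: repeated rounds.** For b baseline and f follow-up rounds, the variance factor is F = [1 + (f − 1)r]/f − b·r²/[1 + (b − 1)r], with the second term zero when b = 0. Effective children per arm: n = (30 × 12/3.9)/F = 92.3/F.

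**Step 3: power.** Φ{[0.10 − 1.96·√(2 × 0.20 × 0.80/n)] / √[(0.25 × 0.75 + 0.15 × 0.85)/n]}.

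**The plan's own figure.** With b = 1 and f = 4, F = 0.643 − 0.274 = 0.368, n = 250.5, and power is 80.1% (80.5% with an unpooled variance). The usual formula needs 250 per arm, so the stated 80% is reproduced.

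**The effect at one visit, same inputs.**

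| Baseline rounds | F | n per arm | Power, 25% v 15% |
|---|---|---|---|
| 0 | 1.000 | 92.3 | 40% |
| 1 | 0.726 | 127.2 | 51% (52% unpooled) |
| 2 | 0.640 | 144.3 | 57% |

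The smallest reduction detectable with 80% power is then 54% with one baseline round and 51% with two, against the stated 40%. More baseline rounds do not close the gap. As b grows, F tends to 1 − r = 0.476, so n tends to 194 and power to about 69%.

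**Other stated effects.** For mean pathogen counts, one baseline and four follow-up rounds give 76% power (31% reduction, mean 1.0) and 78% (23% reduction, mean 2.0), close to 80%. One follow-up round gives 47% and 49%. For inflammation and AMR, 0.30 SD is reproduced with one baseline and two follow-up rounds (0.301 SD using t quantiles on 22 degrees of freedom). One visit alone gives a detectable difference of 0.33 to 0.41 SD (normal quantiles, two to no baseline rounds).

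**What visit-specific reporting could show.** Variance of a settlement mean = 3.9/30 = 0.130; covariance between visits = (0.10 + 29 × 0.067)/30 = 0.0681. Without baseline adjustment, a one-visit effect has SE √(2 × 0.130/12) = 0.147 SD, so an interval of about ±0.29 SD. The change in effect between 6 and 24 months has SE √[4 × (0.130 − 0.0681)/12] = 0.144 SD. Power for a change of 0.30 SD is Φ(0.30/0.144 − 1.96), about 55%. For the illustration above (15% becoming 20%, about 0.125 SD) it is about 14%.

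**The case against.** The strongest reply is that choosing one primary visit is a legitimate design choice, and that a journal article may leave further contrasts to an analysis plan not shown here. Both points stand. They do not settle the mismatch, because the article itself fixes both the target visit and the power statement, and the two do not describe the same effect.

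A second reply is that the averaged reading was intended throughout. That is plausible, since the 80% is reproduced that way, but the target visit in Statistical analyses then needs rewording. The match is also not proof: the number of baseline rounds is unstated, and two baseline with two follow-up rounds would give 77%.

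A reader might go further, in ways the article does not support:

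- **That the 18- and 24-month samples are unused, or durability untested.** Those rounds enter the primary model, and an unseen plan may contain later contrasts. The most one can say is that this document names none.
- **That the decision to extend the intervention to the controls hangs on the late effect.** The Overview already commits to implementing it there; Study oversight says only that results will inform and optimise that rollout.
- **That the 6-month effect reflects a single season.** No visit dates by settlement are given.
- **That a persistence hypothesis goes unanswered.** The stated hypotheses contain none. The remark "while we intend to monitor the sustainability of the intervention" belongs to a limitation about funding for two years of formal monitoring.

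**Conclusion.** The concern holds as an inconsistency over which effect is primary. Read as an average over 6 to 24 months, the pathogen result has the stated 80% power but the wrong label. Read as the effect at 6 months, it has the right label but about 52% power (40% to 57%), and no randomised effect beyond 12 months is named in this document.

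The figures rest on two-sided 5%, equal settlements, no dropout and none to two baseline rounds. Reading the same-child 0.10 as an autocorrelation instead raises r to 0.538 and moves power by about one percentage point. Unequal settlements, dropout or t quantiles would lower power under both readings, so they do not explain the gap. The conclusion does not extend to a claim that durability has been neglected.

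**What to change.** 1. In Statistical analyses, state whether the primary pathogen effect is the 6-to-24-month average or the visit-specific effect at 6 months, and whether the primary GEE has one arm term or arm-by-visit terms. Do the same for the 12-month target for AMR and inflammation.
2. Align Sample size with that choice. If the effect is visit-specific, restate the power or the detectable reduction, with the number of baseline rounds and the significance level used.
3. As a secondary analysis, fit arm-by-visit terms and report each primary outcome's effect with its confidence interval at 6, 12, 18 and 24 months. Name the 24-month effect as secondary and the 6-to-24-month change as descriptive.

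The cost is wording and one additional model fit, with no new visits, samples or assays. The downside is more estimates with wide intervals (about ±0.3 SD per visit) and low power for the change. The text should say that these results cannot support a claim of primary success or show that the effect persists.

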**Methods and analysis:**

RISE is a cluster randomised controlled trial among 12 settlements in Makassar, Indonesia, and 12 in Suva, Fiji. Six settlements in each country have been randomised to receive the intervention at the outset; the remainder will serve as controls and be offered intervention delivery after trial completion. The intervention involves a water-sensitive approach, delivering site-specific, modular, decentralised infrastructure primarily aimed at improving health by decreasing exposure to environmental faecal contamination. Consenting households within each informal settlement site have been enrolled, with longitudinal assessment to involve health and well-being surveys, and human and environmental sampling. Primary outcomes will be evaluated in children under 5 years of age and include prevalence and diversity of gastrointestinal pathogens, abundance and diversity of antimicrobial resistance (AMR) genes in gastrointestinal microorganisms and markers of gastrointestinal inflammation. Diverse secondary outcomes include changes in microbial contamination; abundance and diversity of pathogens and AMR genes in environmental samples; impacts on ecological biodiversity and microclimates; mosquito vector abundance; anthropometric assessments, nutrition markers and systemic inflammation in children; caregiver-reported and self-reported health symptoms and healthcare utilisation; and measures of individual and community psychological, emotional and economic well-being. The study aims to provide proof-of-concept evidence to inform policies on upgrading of informal settlements to improve environments and human health and well-being.

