### Study settings

The study is being conducted across two countries where large portions of the population are subject to inadequate water and sanitation infrastructure. Indonesia and Fiji were purposively selected to represent a diversity of characteristics across the Asia-Pacific, which might influence intervention effects, including climatic factors, water security, tidal inundations, population density, sanitation practices, and socioeconomic and cultural conditions. Within each country, candidate sites were selected in consultation with local government authorities, intervention funders, research partners, communities and other organisational stakeholders. Formative work consisted of four phases: (1) extensive reconnaissance visits to both cities to understand the range of site conditions and to scope potentially suitable sites; (2) early engagement with local and national governments to determine priorities and preferences, and to ascertain tenure status for each site; (3) household enumeration surveys to determine approximate population size and demographics in each settlement and (4) extensive discussions with community leaders and residents to determine their willingness to participate and priorities.

Makassar, the provincial capital of South Sulawesi, has seen rapid urbanisation and population growth in the last decade, with unplanned city growth resulting in a dramatic rise of informal settlements. The 12 settlements of the RISE project are dispersed across the city and represent a diversity of settlement typologies. While the settlements are located in various flood plains and coastal areas, they are all characterised by dense and precariously built housing, little open space, poor vehicular and pedestrian access, and water stressors. Water bodies and soil are typically contaminated with solid waste derived from animal and human sources, and with domestic black and grey wastewater. Seasonal and other flooding is common, requiring makeshift planking for access. Despite some variation in socioeconomic status within and across settlements, sites typically house the most economically vulnerable populations. Households across the settlements predominantly live on small parcels of privately owned land often with one house, or in some instances two or three houses occupied by extended family groups, with varying degrees of land tenure security.

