### Randomisation

Randomisation was performed separately for each city: March 2019 in Makassar and November 2019 in Suva (figure 2). Randomisation occurred following settlement recruitment and completion of 12 months of baseline surveys. Settlements (clusters) have been randomly assigned to either intervention or control groups, with equal numbers in each group. Covariate-constrained randomisation was utilised using the cycrand package in Stata V.15 to achieve balance between the intervention and control groups on key baseline factors determined a priori.

For Makassar, intervention and control groups were first balanced on number of children aged under 5 years (four settlements in each group: ≤10, 11–30 and >30 children) and flood risk (high and low, six settlements in each), producing 90 allocations. Subsequently, the 30 allocations most imbalanced on average asset score were removed, with the score determined from each household’s ownership of selected assets. For Suva, intervention and control groups were first balanced on number of children aged under 5 years (<40 children, eight settlements; >40 children, four settlements) and flood risk and site contamination grouping (two extreme risk, two high risk, and eight medium risk settlements). This resulted in 120 allocations, from which the 30 most imbalanced allocations of asset score were removed, followed by the 30 most imbalanced allocations of average number of children under 5 years. For each of the cities, this resulted in the 60 best balanced allocations being used for the randomisation (total 3600 (60×60) possible allocations for the trial). A randomisation ceremony was held in both cities, where a child from the pilot community selected a ping pong ball from a large glass jar that contained 60 ping pong balls numbered 1–60, representing the 60 determined random allocations that achieved the balance criteria specified above.

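### City, the randomisation stratum, is missing from the covariate list for all models, and flood risk category means different things in the two cities; standard errors may be conservative if outcomes differ by city

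*Protocol article*

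**What the plan says.** The Randomisation section of the Protocol article says: "Randomisation was performed separately for each city: March 2019 in Makassar and November 2019 in Suva". The abstract confirms the split: "Six settlements in each country have been randomised to receive the intervention at the outset". City is therefore the stratum within which allocation was drawn.

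The Statistical analyses section then gives an explicit list for every model: "All models will adjust for the baseline covariates, number of children under 5 years, flood risk category (see Randomisation section) and asset score". For temporal adjustment it adds "indicator variables for seasonal patterns (eg, rainy vs dry), local rainfall data for each site and an indicator term for any major flood event". Neither list contains city or country.

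The cross-reference for flood risk leads back to two different gradings. Makassar used "flood risk (high and low, six settlements in each" group. Suva used a joint grouping of flood risk and site contamination: "two extreme risk, two high risk, and eight medium risk settlements". The bands for number of children under 5 also differ: up to 10, 11–30 and over 30 in Makassar; below and above 40 in Suva. No city-specific scale is stated for asset score.

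Study settings gives a reason to expect that the cities differ: "Indonesia and Fiji were purposively selected to represent a diversity of characteristics across the Asia-Pacific, which might influence intervention effects".

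**The concern.** An analysis should normally reflect the restriction built into the allocation. Here the factors balanced within each city are carried into the model, but the stratum above them is not. With six settlements per arm in each city, a between-city difference in outcome cannot tilt the arm comparison. It can still sit in the residuals of a model that ignores city, and the robust standard error would count it as noise although the design has already removed it. Intervals would then be wider than they need be, in a trial with only 24 clusters.

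The second issue is definition. The text does not say how one flood risk variable is formed from the two gradings. *Low* occurs only in Makassar, *medium* and *extreme* only in Suva, and *high* in both with different meanings. How much of the city difference the model absorbs depends on that unstated coding.

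**Working it through.** **Inputs from the Protocol article.** 24 settlements, 12 per city, 6:6 within city; on average 30 children per settlement; within-period intracluster correlation 0.10, between-period 0.067, same child 0.10; baseline prevalence 25%; 80% power for 0.30 SD at 12 months (Sample size section).

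**Assumptions, not in the documents.** The Makassar–Suva outcome gap *d*; two-sided alpha of 0.05; a one-visit comparison of settlement means on the risk-difference scale, without adjustment for the baseline outcome, as an approximation to the planned log-link model.

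**1. The plan's own power figure.**
- Design effect = 1 + 29 × 0.10 = 3.9.
- Same-child correlation beyond the cluster = (0.10 − 0.067)/0.90 = 0.037.
- Correlation of settlement means over time: r = (30 × 0.067 + 0.90 × 0.037)/3.9 = 0.524.
- With one baseline and two follow-ups, the variance factor = (1 + r)/2 − r² = 0.488.
- SE = √(2 × 3.9/360 × 0.488) = 0.103 SD.
- Power for 0.30 SD = 79.7% (t, 22 df) or 83.1% (normal). The stated 80% is reproduced by pooling both cities, 12 settlements per arm.

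**2. Variance of a settlement mean at one visit.** 0.25 × 0.75 × (0.10 + 0.90/30) = 0.1875 × 0.13 = 0.0244.

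**3. How much city variation the flood labels leave.** Code city as ±½. Its total sum of squares over 24 settlements is 24 × ¼ = 6.
- *Four shared labels (low, medium, high, extreme).* Low, medium and extreme identify the city for 6 + 8 + 2 = 16 settlements. Only *high* is mixed, and leaves 6 × 2/8 = 1.5. The share left is 1.5/6 = 25%.
- *Five city-specific levels.* These span city completely; the share left is 0.
- *Nothing absorbed.* The share left is 1; this is an upper bound.

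**4. Inflation of the reported SE.** Ratio = √(1 + share × (d/2)²/0.0244).

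| Gap d | Nothing absorbed | Four shared labels | City-specific levels |
|---|---|---|---|
| 0 | 1.00 | 1.00 | 1.00 |
| 10 points | √(1 + 0.0025/0.0244) = 1.05 | √(1 + 0.000625/0.0244) = 1.01 | 1.00 |
| 20 points | √(1 + 0.0100/0.0244) = 1.19 | √(1 + 0.0025/0.0244) = 1.05 | 1.00 |

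The outcome SD is √0.1875 = 0.433, so these gaps are about 0.23 and 0.46 SD.

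**5. Check by simulation.** 3000 settlement-level trials per scenario were run with all three listed covariates and four flood labels. Reported-to-true SE ratios were 1.00 at d = 0 and at 0.25 SD, 1.07 at 0.5 SD and 1.24 at 1.0 SD (type I error 1.9% in the last case). Adding city brought the ratio back to about 1.0. Child counts and asset scores were invented within the stated bands, the final exclusions down to 60 allocations were not applied, an HC2-type correction stood in for the cited small-sample method, and local rainfall was not simulated.

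**6. Power.** Start from 80% and leave the true SE unchanged: power = Φ(1.96 + 0.84 − 1.96 × ratio). Ratios of 1.01, 1.05 and 1.19 give about 79%, 77% and 68%. This treats the intracluster correlation of 0.10 as wholly within-city.

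**The case against.** The strongest reply is that the inflation may be nil. The list refers to flood risk category as defined in the Randomisation section, and that section defines it city by city. Taken literally, this gives five city-specific levels, which make a city term redundant. Coding of a covariate is also detail that an article commonly leaves to the analysis plan, which is not shown. This stands as far as it goes: the text does not fix the pooled coding. Nor does it fix the city-specific one, and a list given for all models that omits the stratum is a statement, not a silence.

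Several stronger readings are tempting but not supported:
- *That the standard errors are too large, without condition.* This needs a between-city difference, which the documents do not give, and a coding that leaves part of it unabsorbed.
- *That the differing flood scales cause the inflation.* They work partly the other way: the labels alone identify the city for 16 of 24 settlements. Their cost is that the *high* level has no single meaning.
- *That all the listed covariates are on different scales.* This is shown for flood risk and for the child-number bands used in randomisation. The model names the number of children, which may enter as a count, and asset score has no stated city-specific scale.
- *That the loss should be judged on an average over four visits.* The planned effect is estimated at 6 months for pathogens and at 12 months for antimicrobial resistance and inflammation markers.
- *That the stated 80% power is wrong.* The article does not say whether the correlation of 0.10 already includes between-city variation. If it does, the stated power does not depend on a city term.

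Site-level rainfall, also in the models, may absorb more of the city difference.

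**Conclusion.** The point holds in a limited form. City is the randomisation stratum and is absent from the covariates prescribed for all models, and flood risk category is not one variable across the two cities. The effect estimate is not biased, because arms are balanced 6:6 within each city, and any error is conservative. It costs precision, not validity.

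The size is conditional on the assumed gap and on the coding. For the 10–20 point range at a single visit, the likely loss under shared labels is small, the 5–19% figure is an upper bound that requires the planned flood adjustment to absorb nothing, and city-specific coding removes the problem. The change is still worth making: it is nearly free, and it stops precision from depending on a coding choice that the article does not state.

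**What to change.** In Statistical analyses, add city as a fixed effect to every effect model and state that flood risk category is defined within city (high/low in Makassar; extreme/high/medium in Suva). State also whether number of children under 5 enters as a count or as a within-city category.

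The cost is wording plus at most one between-cluster degree of freedom. Four shared labels use 3 degrees of freedom. City plus within-city levels use 1 + 1 + 2 = 4, the same as five city-specific levels, so nothing extra is spent if that coding was already intended.

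City-by-visit terms, a city-by-intervention interaction and city-specific estimates are optional. They are not needed to resolve this point, and they would use further degrees of freedom or precision.
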